### Intervention group

The SIACI program was developed by the research team in consultation with art therapists, neurology experts, and clinical nursing specialists. To ensure standardized administration of the intervention, it will be delivered under the supervision of qualified art therapists by intervention staff who will have received AT training. The intervention staff will be required to complete an intervention-related competency examination before administering the intervention. In each session, the intervention staff will keep a log of the progress and responses of each participant.

AT, with appropriate modifications, is suitable for all dementia phases [27, 47]. Participants with different degrees of CIs will be assigned to different groups corresponding to their ability. The group size will be based on Liebmann’s [48] suggestion that the appropriate number of participants in group activities is 4–12, but if there are experienced group activity facilitators, this can be increased, as long as all participants can maintain visual contact, communicate verbally, and have the opportunity to share and express themselves.

The program will be conducted using neurocognitive function training patterns [49], which integrate bottom-up and top-down approaches (Fig. 2). The program will be divided into three modules, i.e., art experience, art enlightenment, and art exploration, which correspond to the three stages of cognition regulation (perception, comprehension, and application). The AT-based cognitive intervention sessions will be based on the theoretical frameworks of media dimension variables (MDV) (Fig. 2A) and expressive therapies continuum (ETC) (Fig. 2B) [50–53]. The activities will include but not be limited to the following diverse artistic expressive forms: performance arts (music, drama, and dance), visual arts (painting, collage, knitting, sculpture, and pottery), literary arts (novel-writing, poetry, other forms of text-related activities), and the huge range of applied arts (art design, architectural design, and industrial art). Each session will follow the principles of individualization, changing the difficulty/cognitive level from simple to complex, changing the activity structure from highly structured to semi-structured or freestyle, and timely adjustments to adapt to and gradually improve cognitive function.

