#### Sample size determination

The required sample size was estimated using PASS v11.0 (NCSS, Kaysville, UT, USA) based on a completely random design for comparing the means of two independent samples. To our knowledge, there is no previous study on a comprehensive intervention for CIs among older adults in mainland China, so we estimated the effect size of one of the primary outcomes (general cognitive function) based on our previous study that used creative expression therapy to improve MCI patients’ cognitive function [46] . The study was like the planned trial in some respects, as both are RCTs, one of the primary outcomes is general cognitive function, and one of the primary outcome measurement tools (MoCA) is the same. Our previous study [46] found MoCA scores of 24.68 ± 1.84 and 23.13 ± 1.68 in the intervention and control groups, respectively. A sample size of 35 participants per group was determined to be sufficient to detect an effect with a type 1 error rate of 5% (α = 0.05) and 95% power (β = 0.05). Taking into consideration a 20% attrition rate, a total of 88 participants will be needed, with 44 participants per group.

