### Data collection and analysis

All data analysis will be performed using SPSS Statistics v22.0 (IBM). To ensure that the outcome assessors and data analysts are blinded to group assignment, they will not interact with the participants except, in the case of outcome assessors, during data collection. Demographic and other baseline characteristics will be summarized using descriptive statistics. If necessary, the results will be adjusted for potential confounders, such as age, gender, and education. Between- and within-subject comparisons of the neuropsychological test scores and other outcomes will be conducted using repeated-measures analysis of variance (ANOVA). Statistical analyses will be based on an intention-to-treat (ITT) approach [65], missing data will be imputed by multiple imputation. *P* < 0.05 for two-tailed tests will be considered significant. In sensitivity analyses, we will perform per-protocol (PP) analyses [66], including only the participants who completed the SIACI program and outcome assessment. The details of the fMRI data analysis are displayed in the Additional file.

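### SIACI is delivered in shared therapy groups and the control arm is ungrouped, but the sizing and the named analysis treat all participants as independent, so between-arm standard errors are too small wherever group delivery induces correlation

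*Protocol article*

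**What the plan says.** Randomisation is individual and 1:1 (Randomisation, allocation concealment, and blinding).

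SIACI is a group programme. Under Intervention group, "Participants with different degrees of CIs will be assigned to different groups corresponding to their ability", and the size guide is that "the appropriate number of participants in group activities is 4–12", with larger groups allowed when facilitators are experienced. Members get to know each other, create work and discuss it together at each session. The COVID-19 contingency keeps the exchange going through WeChat groups. Under Waitlist control group, controls simply carry on with their usual activities.

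Under Sample size determination, the calculation is "based on a completely random design for comparing the means of two independent samples", and "A sample size of 35 participants per group was determined to be sufficient to detect an effect" with 95% power, raised to 44 per arm for 20% attrition. Under Data collection and analysis, "Between- and within-subject comparisons of the neuropsychological test scores and other outcomes will be conducted using repeated-measures analysis of variance (ANOVA"), with adjustment for confounders such as age, gender and education if necessary. Neither section has an ICC, a design effect, or a therapy-group or facilitator term.

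**The concern.** This is a partially nested design: participants in one arm are nested in therapy groups and those in the other are not. Members of a therapy group share 24 sessions, the same peers and possibly the same facilitator. If that makes their outcomes more alike, the mean of the SIACI arm varies more than the same number of independent people would imply. A two-sample calculation or an ANOVA on individuals misses this extra variance, so confidence intervals are too narrow and P values too small.

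At stake is the error rate of the between-arm tests on the five primary scales (MoCA, MMSE, GDS, SAS, QoL-AD) and on any other outcome affected in the same way. The generous 95% power does not cure this, because an inflated type 1 error does not shrink when power is high.

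**Working it through.** **Inputs**
- MoCA results of the earlier trial (Sample size determination): "24.68 ± 1.84 and 23.13 ± 1.68 in the intervention and control groups". Difference 24.68 − 23.13 = 1.55. Pooled SD = √((1.84² + 1.68²)/2) = √3.104 = 1.762. Standardised difference 1.55/1.762 = 0.880.
- Type 1 error 5%, two-sided. The sizing section gives the 5%; Data collection and analysis says that P < 0.05 "for two-tailed tests will be considered significant".
- Group size m = 4, 8 and 12: the two ends and the midpoint of the article's range.
- ICC = 0.01, 0.05 and 0.10. This is an assumption; the article gives none.

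**1. The plan's own figure.** Normal approximation: 2 × (1.762 × (1.960 + 1.645)/1.55)² = 33.6, so 34 per arm. With the noncentral t distribution, power is 94.7% at 34 and 95.2% at 35, so 35 per arm is reproduced. Then 35/0.80 = 43.75, rounded up to 44 per arm and 88 in total. A one-sided normal calculation gives 28 and does not match. The figures reproduce under full independence, so they contain no allowance for grouping.

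**2. Clustering in one arm.** With equal total variance in the arms:
- design effect in the SIACI arm: DE = 1 + (m − 1) × ICC
- true SE divided by assumed SE: R = √((1 + DE)/2)
- true two-sided error: 2 × (1 − Φ(1.960/R))
- power: noncentral t with noncentrality 0.880 × √(n/2)/R and 2n − 2 degrees of freedom.

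Worked case, m = 8 and ICC = 0.05: DE = 1 + 7 × 0.05 = 1.35; R = √(2.35/2) = 1.084; 1.960/1.084 = 1.808; true error 7.1%.

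| m | ICC | DE | R | True error | Power, 35 per arm | Power, 44 per arm |
|---|---|---|---|---|---|---|
| 4 | 0.01 | 1.03 | 1.007 | 5.2% | 95% | 98% |
| 4 | 0.05 | 1.15 | 1.037 | 5.9% | 94% | 98% |
| 4 | 0.10 | 1.30 | 1.072 | 6.8% | 92% | 97% |
| 8 | 0.01 | 1.07 | 1.017 | 5.4% | 95% | 98% |
| 8 | 0.05 | 1.35 | 1.084 | 7.1% | 92% | 96% |
| 8 | 0.10 | 1.70 | 1.162 | 9.2% | 88% | 94% |
| 12 | 0.01 | 1.11 | 1.027 | 5.6% | 94% | 98% |
| 12 | 0.05 | 1.55 | 1.129 | 8.3% | 89% | 95% |
| 12 | 0.10 | 2.10 | 1.245 | 11.5% | 83% | 91% |

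The power columns ignore the few degrees of freedom for the group variance, so they are slightly generous.

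**3. Simulation, 35 per arm, 20,000 runs per setting.** On post-treatment scores at ICC 0.05, the error is 7.4% (m = 8) and 8.1% (m = 12), in line with the table. On change scores, with an assumed baseline–post correlation of 0.7, it is 8.9% and 10.6%. It is higher there because the change has only 2 × (1 − 0.7) = 0.6 of the score variance, so a group component of 0.05 becomes 0.05/0.6 = 8.3% of it.

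**4. Ability sorting on its own.** Groups were sorted by ability, ability explained half of the outcome variance, and no group-induced variance was added. The error was 4.7–5.1% for m = 4, 8 and 12. Individual randomisation leaves the same spread of ability in both arms, so the ordinary test already counts it.

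**The case against.** The strongest objection is that everything depends on an ICC that the article does not give. At 0.01 the error is 5.2–5.6%, which is close to nominal. Error exceeds 5% only if the average effect is zero and therapy groups nevertheless differ; if the sessions change nothing, they induce no group variance and the rate stays at 5%. Standardised training, a competency examination, individual tailoring and home delivery during outbreaks could all keep the ICC low. Shared staff add correlation only if facilitators differ between groups, which the article does not say. All of this stands. It makes the size uncertain; it does not make independence a safe assumption.

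It can also be said that random-effect structure belongs in the statistical analysis plan, which is not shown. That holds for the details. But the article itself names a sizing model and an analysis model, and both assume independence.

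A reader might infer four stronger claims that the documents do not support:
- *Every between-arm result has inflated error.* Only outcomes with group-induced correlation do, and nothing shows that one ICC carries over to the blood, P300 or MRI measures.
- *Forming groups by ability inflates error.* Step 4 shows that it does not.
- *Controls lack an ability class.* Diagnosis is an inclusion criterion, and eligibility screening and baseline assessment precede randomisation, so every control has a diagnosis and baseline scores to adjust for.
- *The trial is underpowered.* Only the most adverse settings at 35 per arm fall below 90%. If attrition also shrinks groups of 12 to 12 × 0.8 = 9.6, the lowest figure rises to about 87% by the normal approximation.

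**Conclusion.** The point holds as a conditional one. The sizing and the ANOVA ignore a grouping that the article itself builds into one arm, and the between-arm standard error is understated wherever that grouping induces correlation. Over the assumed ICC range the understatement is a factor of 1.01 to 1.25. The excess error is negligible at the low end and material from about ICC 0.05 with groups of 8 to 12, or in larger groups, which the article allows. The analysis model should be changed; the loss of power is not a reason to enlarge the trial.

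Ability-based grouping matters in one respect only. A raw ICC across groups sorted by ability would mix severity with the shared-delivery effect and over-correct, so the group effect has to be estimated conditional on severity.

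**What to change.** 1. Record therapy-group ID and facilitator for every SIACI participant. Recruitment is already under way, but staff must keep session logs, which should allow this to be filled in for anyone already treated.
2. For between-arm comparisons, replace the repeated-measures ANOVA with a pre-specified mixed model: a random therapy-group effect in the SIACI arm only, fixed effects for pre-randomisation diagnosis and baseline score, the repeated measures on each participant, and Satterthwaite or Kenward-Roger degrees of freedom.
3. Restate the 95% power over a stated range of ICC and group size, and give the assumed values.

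Costs: intervals become somewhat wider. The group variance rests on few groups, from about 44/12, so 4, to 44/4 = 11, and will be imprecise. Group IDs exist in one arm only and so reveal allocation; the model must be fixed before the blinded analysts see them. No extra enrolment is needed if the power statement is revised. Keeping 95% instead would need (1 + DE) × (1.762 × 3.605/1.55)² per arm, rounded up, plus one for the t distribution, then divided by 0.80: 45–50 (m = 4), 45–59 (m = 8) or 47–68 (m = 12) per arm, against 44.

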**Fig. 2 Fig2:**
[figure not shown]
Overview of the framework of SIACI program. **a** The framework of SIACI program. **b** The activity process of SIACI program

There will be four main activity processes in each session. Firstly, the activity will be introduced to let the participants get to know each other and the purpose, meaning, and content of the activity. Secondly, the participants will be asked to participate in various warm-up activities related to the activity theme, get familiar with the activity materials, and/or have an activity theme-related discussion before the art creation. Thirdly, they will be asked to create anything they want that they think is relevant to the theme for each session. Finally, they will be asked to share their creations and their feelings and perspectives to help them to gain insights and discuss their feelings. The framework of the SIACI program is shown in Fig. 2.

If there is a COVID-19 outbreak in the area or nearby area during the intervention period, and it is therefore necessary to stop the group AT activities, an intervention contingency plan will be carried out. A package containing the activity-related materials will be mailed to each participant’s home, WeChat software (which is the most widely used social media app among older adults in China) will be used as the medium to introduce the activity theme, material descriptions, and other related information, and WeChat groups will be used to communicate and to share the resultant art works. If a participant cannot use a device to access WeChat (such as a smartphone, iPad) or use WeChat itself, they will receive the required information (the activity theme, material descriptions, and other related information) in paper form and, if necessary, they will receive communication and guidance by phone. Their art works will then be shared when the group art activities are resumed in person, to ensure the ongoing implementation of the intervention as far as possible.

### Waitlist control group

Following baseline assessment, participants in the waitlist control group will engage in their usual activities during the 16-week study period. After the study, if the SIACI program leads to significant improvements in cognitive function, these participants will be offered the program as a courtesy for their participation.

### Outcome measures

To explore the effects and mechanisms of SIACI, various measurements will be obtained at baseline, immediately after the intervention, and at the 6-month follow-up. Outcome measures will include neuropsychological assessments, blood biomarkers, ERP-P300, and MRI parameters. All outcome measures and assessment time points are shown in Table 1. The outcomes will be assessed by experienced staff members who will be blinded to group allocation throughout the study.

**Table 1 Tab1:**
[figure not shown]
SIACI outcome measures

#### Demographic and other baseline characteristics

To determine whether demographic and other baseline variables are confounding factors that affect the outcome variables, basic demographic data (e.g., age, gender, religion, marital status, education, occupation, and socioeconomic status), history of disease, medication use, and leisure activities will be collected from participants via a questionnaire at baseline.

#### Neuropsychological assessments

##### Primary outcome measures

The primary outcome measures will be general cognitive function and psychological indicators, as measured by the Chinese versions of MoCA, MMSE, Geriatric Depression Scale (GDS) [54], Zung Self-Rating Anxiety Scale (SAS) [55], and Quality of Life in Alzheimer’s Disease scale (QoL-AD) [56].

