#### Randomisation, allocation concealment, and blinding

Ensuring allocation concealment, participants will be randomized (after obtaining written informed consent, eligibility screening, and baseline assessment) to the SIACI and waitlist control groups at a 1:1 ratio by a study staff member (who will not be involved in participant recruitment or outcome assessment) using Research Randomizer software (http://www.randomizer.org/). The participants will then be told their group assignment by the intervention staff. Due to the nature of non-pharmacological interventions, only the outcome assessors and data analysts (not the participants or intervention staff) will be blinded to group allocation.

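### Five unranked primary scales share one unadjusted 0.05 threshold, while the 5% error rate and 95% power were set for a single MoCA comparison

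*Protocol article*

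**What the plan says.** - **Primary outcomes** (Primary outcome measures): "The primary outcome measures will be general cognitive function and psychological indicators, as measured by the Chinese versions of MoCA, MMSE", then GDS, SAS "and Quality of Life in Alzheimer’s Disease scale (QoL-AD"). That makes five scales. None is ranked above the others.
- **Timing** (Outcome measures): "various measurements will be obtained at baseline, immediately after the intervention, and at the 6-month follow-up". The text does not call either post-baseline visit primary.
- **Analysis** (Data collection and analysis): "Between- and within-subject comparisons of the neuropsychological test scores and other outcomes will be conducted using repeated-measures analysis of variance (ANOVA"). No contrast is singled out as the deciding one.
- **Threshold** (same section): P < "0.05 for two-tailed tests will be considered significant". No adjustment or testing order qualifies this, and no rule says that all five must succeed.
- **Sample size** (Sample size determination): "so we estimated the effect size of one of the primary outcomes (general cognitive function"). It uses MoCA results from an earlier trial by the same team (24.68 ± 1.84 against 23.13 ± 1.68), a 5% type 1 error and 95% power. This gives 35 per group, raised to 44 per group (88 in total) for 20% attrition.

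**The concern.** The 5% error rate in the sample size section belongs to one comparison on one scale. The analysis rule lets any of five primary scales reach significance at that same level. As written, the trial can report a positive primary result in five ways, each carrying its own 5% risk, so the chance that an ineffective programme yields at least one is well above 5%. The power statement is likewise specific to MoCA and says nothing about the other four scales.

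The article is also not settled on what is central. The Abstract places quality of life, anxiety and depression among other health-related outcomes, alongside sleep and physical activity. The Methods make those three primary and leave sleep and physical activity secondary. The hypothesis at the end of the Background concerns neurocognitive performance. A reader of the final report could not tell which result was meant to decide the question.

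**Working it through.** **1. The plan's own figure.** Inputs are from Sample size determination.

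- Difference: 24.68 − 23.13 = 1.55.
- Pooled SD: √((1.84² + 1.68²)/2) = √3.104 = 1.762.
- Standardised difference: 1.55/1.762 = 0.880.
- Normal approximation, two-sided 0.05, 95% power: n = 2(1.960 + 1.645)²/0.880² ≈ 33.6, so 34 per group.
- Noncentral t: power is 94.7% at 34 and 95.2% at 35, so 35 per group.
- Attrition: 35/0.80 = 43.75, so 44 per group and 88 in total.

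The stated figure is reproduced. It is correct for one MoCA comparison at 0.05.

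**2. Error across five scales, one test each.** If the tests are independent: 1 − 0.95⁵ = 22.6%. Between-scale correlations are not in the article, so they are assumed here (equal correlation, no true effect on any scale):

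| Assumed between-scale correlation | Five normal tests (200,000 runs) | Group-by-time test in repeated-measures ANOVA, 35 per arm (20,000 runs) |
|---|---|---|
| 0 | 22.5% | 23% |
| 0.3 | 21% | 21% |
| 0.5 | 18% | 19% |
| 0.7 | 15% | 15% |

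This gives the range of about 15–23%.

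**3. If each scale is tested at both post-baseline visits.** There are then ten tests. The between-visit correlation is also assumed, from 0.5 to 0.9:

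| Between-scale correlation | Visit correlation 0.5 | Visit correlation 0.9 |
|---|---|---|
| 0 | 37.8% | 30.6% |
| 0.3 | 35.4% | 28.2% |
| 0.5 | 31.2% | 24.6% |
| 0.7 | 25.6% | 20.2% |

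This gives the range of about 20–38%.

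**4. What the remedies do.**

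- One primary scale, contrast and time point: error 5%, 88 participants, MoCA power 95.2% with 35 completers per arm.
- Holm over five tests: the strictest step is 0.05/5 = 0.01. MoCA is therefore tested at 0.01 at worst. With 35 per arm the noncentrality is 0.880 × √(35/2) = 3.68 on 68 degrees of freedom, and power is 84.5%.
- Keeping 95% power at 0.01 would take 48 completers per arm: 48/0.80 = 60 randomised per arm, 120 in total.
- If both visits stayed in the family, the strictest step would be 0.05/10 = 0.005 and MoCA power 77.8%. This is why Holm across five needs exactly one contrast per scale.

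**The case against.** **An analysis plan may deal with it.** Multiplicity methods and exact contrasts are often left to a statistical analysis plan, which is not shown. The outcome table is not visible either, and could mark a primary time point. This stands as far as it goes: the absence of an adjustment method or a named visit is not in itself a fault here. But the article does state which outcomes are primary and which threshold applies, and those statements together give a wrong error rate for the primary conclusion.

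**Ten tests.** A reader might infer that every scale is tested at every visit, and quote 40% (1 − 0.95¹⁰) or a figure in the thirties as the trial's error rate. The article does not say that. It names repeated-measures ANOVA, most naturally read as one group-by-time test per scale. The higher range applies only if visits are tested separately.

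**Unblinded ratings.** Participants know their allocation: "only the outcome assessors and data analysts (not the participants or intervention staff) will be blinded to group allocation". A reader might infer that the three psychological scales are all self-rated and so open to expectation effects. Only SAS is shown to be self-rated, by its name. The article does not say how GDS and QoL-AD are administered, so that claim is not supported for them.

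**Cognitive claims are narrower.** The hypothesis and the offer of the programme to controls turn on cognition, so a positive mood scale alone would not support them. That is fair. Yet with MoCA and MMSE alone the figure is still up to 1 − 0.95² = 9.75% if independent, and the article does not restrict primary success to those two.

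**Conclusion.** The point holds in a bounded form. Applied as written, the rule gives about a 15–23% chance of at least one significant primary result under no effect, three to more than four times the 5% used for sizing. This rests on one group-by-time test per scale and assumed between-scale correlations of 0.7 down to 0. If each scale is tested at both post-baseline visits, the figure is about 20–38% over the same correlations, with an assumed between-visit correlation of 0.5–0.9. Since no correlations are given, both are conditional ranges and not properties of the trial. The sample size arithmetic is right for the single comparison that it describes. These figures cover chance alone; no estimate of rating bias is made or needed.

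**What to change.** Issue a dated amendment before any unblinded analysis, choosing one of two routes.

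1. **One primary.** Name one primary outcome, one contrast and one time point. MoCA is the natural choice because the trial is sized on it, and immediately after the intervention is a reasonable time point. The other four scales and all 6-month results become secondary. Cost: no extra participants and no loss of the stated power, but four scales lose primary status in a trial already recruiting. That is a substantive change and should be declared as one.
2. **Five primaries with Holm.** Keep all five, pre-specify one contrast per scale, and apply Holm across the five. Cost: with 35 completers per arm, MoCA power may fall from 95% to no lower than about 84%, and the stated power should be revised to match. Holding 95% at the strictest step would mean 120 randomised instead of 88.

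Under either route, the Abstract's grouping of outcomes should be brought into line with the Methods.
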